### Randomization and Blinding

After completion of the informed consent and baseline measures, participants will be randomly assigned into one of 2 groups: G1, receiving the regular I-TOPS treatment, or G2, receiving the active control training, namely, the wellness treatment. In detail, the randomization will be conducted by a researcher of the Institute, independently from the research staff responsible for recruiting participants. Randomization of patient assignment to the groups will follow a coin flip procedure using the randomization tool of Microsoft Excel: an automated number will be randomly associated with any recruited patient and determine assignment to G1 (0-0.49) or G2 (0.50-1). No stratification will be used. The independent researcher will give the staff members responsible for the study ([name]) a sealed envelope containing the participant’s group assignment to keep it concealed from the research staff. This is to avoid selection bias and to prevent the research staff from subverting the allocation sequence. In turn, the research staff will give this envelope to the psychotherapists supervising the interventions, who will contact parents of enrolled adolescents to provide information regarding the next study steps on the basis of the group allocation. Indeed, to allow for clinical supervision, treatment fidelity, and patient interactions, the supervising psychotherapist will be required to receive group allocation information. Other research staff, participants, and testers will remain blinded to group assignment. Given these considerations, this study will constitute a double-blinded RCT. Emergency unblinding will be used only in front of reasonable request by the patient or the referring physician due to clinical reasons.

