### Sample Size and Power Calculation

A previous meta-analysis on the effects of the original American TOPS program on the various outcomes found a small-to-medium average effect size (Hedges *g*=0.37) [37]; however, high variability was found among the effect sizes of the different studies analyzed. This led us, to be conservative, to estimate a small effect size of f=0.2 for the evaluation of the power calculation in the present study. Power analysis was conducted using G*Power3 Software (Heinrich-Heine-Universität Düsseldorf) [72,73]. Assuming a correlation of 0.50 between repeated measures and setting the α level at *P*<.05, a sample size of 21 participants per group will be required to obtain 80% of power with our 2 group- and 3 time-point- design. Therefore, a whole sample of 42 participants will be required to be included in the study. Attrition was not considered in performing power calculation, as adherence rates will be a core outcome of this study, which is pioneering for the Italian context and, therefore, will be aimed at collecting data on feasibility. Therefore, any eventual dropouts will be accounted for in statistical analyses using intention-to-treat analysis procedures.

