### Data Analysis Plan

All randomized adolescents will be included in the analyses, irrespective of adherence to treatment in the I-TOPS or wellness intervention. No imputation of a missing baseline or follow-up data will be performed. The *t* tests and chi-square analyses will be performed to compare the I-TOPS (ie, experimental) and wellness (ie, control) intervention groups on continuous and dichotomous variables, respectively. Similar analyses will be performed to examine baseline differences between patients who will complete the study and those who will drop out. Frequencies and means related to feasibility outcomes will be calculated. Analyses will be performed using SPSS (version 29.0.1.0; IBM Corp) [74].

Efficacy outcome measures will be separately entered into linear mixed effect models with “time” (baseline vs immediately after treatment vs 6-month follow-up) and “treatment” (regular I-TOPS vs wellness intervention) and their interaction as fixed factors and “intercepts” and “participants” as random factors. In case of differences in any clinical or demographic variables between groups at baseline, those measures will be included in the analyses as covariates. Mixed model analysis allows flexible modeling of the pattern of change over time and uses all the data for a given participant, even if that participant is not seen at all assessments, allowing us to retain participants with missing assessments. Significant interaction effects (ie, time and group) or group effects will be analyzed by post hoc tests. The significance threshold will be set at <.05. No interim analysis will be planned.

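### A group main effect that averages in the pre-randomisation baseline can trigger efficacy follow-up; the interaction is valid but less precise than a baseline-adjusted contrast

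*Protocol article*

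**What the plan says.** Under Data Analysis Plan in the protocol article, each efficacy outcome goes into a linear mixed model. Time has three levels ("baseline vs immediately after treatment vs 6-month follow-up"), so the baseline score is part of the response. The remaining terms are treatment "and their interaction as fixed factors and “intercepts” and “participants” as random factors". Nothing holds the two baseline means equal, so each arm has its own.

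The rule for what is followed up is "Significant interaction effects (ie, time and group) or group effects will be analyzed by post hoc tests". The threshold is a single one: "The significance threshold will be set at <.05".

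The only baseline adjustment is conditional: "In case of differences in any clinical or demographic variables between groups at baseline, those measures will be included in the analyses as covariates". The baseline value of the outcome is not named there.

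Under Randomization and Blinding, baseline measures come before allocation, allocation is an unrestricted coin flip in a spreadsheet, and "No stratification will be used".

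Under Sample Size and Power Calculation, the inputs are f=0.2 ("to estimate a small effect size of f=0.2 for the evaluation of the power calculation in the present study"), "Assuming a correlation of 0.50 between repeated measures", alpha 0.05 and 80% power, giving 21 per group. The same section cites a meta-analytic Hedges g of 0.37.

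**The concern.** T0 is measured before allocation, so any arm difference at T0 is chance. A main effect of group that averages over T0, T1 and T2 mixes that chance difference with the treatment effect and shrinks the treatment effect at the same time. The plan nevertheless lets this effect open the efficacy follow-up, on equal footing with the interaction. With about 21 per arm and no restriction on allocation, sizeable chance imbalance is a realistic event.

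The second issue is precision. Estimating each arm's baseline freely makes the treatment comparison a change-from-baseline comparison. Conditioning on T0, or holding the baseline means equal as randomisation implies, uses the same data with smaller variance. In a trial of 42 participants that gain is worth having.

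**Working it through.** **Inputs.** From the protocol: 21 per arm, correlation rho=0.50, f=0.2, alpha 0.05, g=0.37. My assumptions: outcome SD of 1, equal correlation between all pairs of times, complete data, exactly 21 per arm, and a treatment effect that is the same at T1 and T2. Taking 0.37 as that between-arm difference in SD units is also an assumption.

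**1. The plan's own figure.** For the within-between interaction with N=42 and m=3 times, lambda = f²·N·m/(1−rho) = 0.04·42·3/0.5 = 10.08 with 2 and 80 df. Power is 80.3% (78.2% at N=40), so 42 reproduces. For the group main effect with the same f, lambda = f²·N·m/(1+(m−1)·rho) = 5.04/2 = 2.52 with 1 and 40 df. Power is 34%. The sample size therefore rests on the interaction alone.

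**2. What the group main effect estimates.**
- With a true difference d at T1 and T2 and none at T0, it estimates (0+d+d)/3 = 2d/3.
- With no true effect and a chance baseline difference b, the expected difference at T1 and T2 is rho·b. The main effect then has expectation b/3 + (2/3)·0.5·b = 0.67b. One third enters directly and the rest through the correlation.

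**3. How often imbalance is large.** The standard error of the baseline difference is √(2/21) = 0.31 SD. The probability that it exceeds 0.5 SD in either direction is 2·(1−Φ(0.5/0.3086)) = 10.5%.

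**4. Error rates, simulated under the null (100,000 trials, rho=0.5).**

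| Test | All null trials | Baseline means differ by more than 0.5 SD |
|---|---|---|
| Group main effect | 5.0% | 30% |
| Time-by-group interaction | 5.0% | 13% |
| Baseline-adjusted mean of T1 and T2 | 5.1% | 4.6% |
| Interaction or group | 9.8% | not computed |

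The 9.8% agrees with 1−0.95² = 9.75%. Among null trials with a significant group effect, the mean absolute baseline difference is 0.57 SD, against 0.25 SD over all null trials. The interaction is also affected by imbalance, in the opposite direction: at T1 the change-from-baseline difference has expectation (0.5−1)·b = −0.5b.

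**5. Precision.** Variances per participant, in units of sigma²:
- T1 change: 2(1−rho) = 1.00
- T1 adjusted for T0: 1−rho² = 0.75
- Average of T1 and T2, change: (1+rho)/2 + 1 − 2·rho = 0.75
- Average of T1 and T2, adjusted: (1+rho)/2 − rho² = 0.50
- Mean of all three times: (1+2·rho)/3 = 0.67, with effect 2d/3

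Power for d=0.37 comes from the noncentral t, with noncentrality = effect/√(variance·2/21):

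| Contrast | Noncentrality | Power |
|---|---|---|
| Group main effect | 0.247/√(0.667·2/21) = 0.98 | 16% |
| T1, change | 0.37/√(1.00·2/21) = 1.20 | 22% |
| T1, adjusted | 0.37/√(0.75·2/21) = 1.38 | 27% |
| T1/T2 average, change | 0.37/√(0.75·2/21) = 1.38 | 27% |
| T1/T2 average, adjusted | 0.37/√(0.50·2/21) = 1.70 | 38% |

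For the 2-df interaction, lambda = 21·(d²/3)/0.5 = 1.92 and power is 21%.

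A constant difference of 0.85 SD corresponds to f=0.2. At that size the simulated powers are 59% (group), 80.5% (interaction) and 96% (adjusted average).

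**6. Sensitivity to rho.** The variance saved by adjustment at T1 is 35% at rho=0.3, 25% at 0.5, 15% at 0.7 and 10% at 0.8. Under the null with rho=0.7, the group test rejects 36% of the time when imbalance exceeds 0.5 SD.

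**The case against.** The text does not say that a group effect will be declared efficacy. It sends such an effect to post hoc tests whose content the article does not give. If those tests compare the arms at each time point, they could show that the difference was already present at T0. A reader might also take the 10% as a false-efficacy rate, and the documents do not support that: it is the rate at which follow-up is triggered. If the post hoc tests were by time point, a trigger together with a nominally significant arm difference at T1 or T2 would occur in about 5.2% of null trials (simulated under the same assumptions). The group test on its own also keeps its 5% overall. Its weakness is error given imbalance.

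The interaction should not be called wrong. It is a 5% test, differential change is a legitimate question in a pre-post design, and at the protocol's f=0.2 it has the planned 80%. Preferring a baseline-adjusted contrast over it is a matter of efficiency. Nor does the gain from 21% to 38% apply to separate tests at T1 and T2: it belongs to their average, and T1 alone reaches 27%. Separate adjusted tests at T1 and T2, with success on either, would themselves have an error rate of about 9.4% to 9.7%. Finally, efficacy here is described as preliminary in a phase-2 feasibility trial.

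All of this stands and limits the point. It does not rescue the group main effect, which remains a diluted, imbalance-sensitive contrast placed beside the interaction in the efficacy paragraph. The conditional covariate rule does not repair it either, because it names clinical and demographic variables and not the baseline outcome.

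**Conclusion.** The point holds for the group-effect route and, as an efficiency point, for the handling of baseline. The group main effect estimates two thirds of a constant post-baseline effect, takes in about 0.67 of a chance baseline difference at rho=0.5, and rejects about 30% of true nulls in the roughly 10% of null trials where baseline means differ by more than 0.5 SD. It also adds a second unadjusted trigger per outcome, and it is not the test on which N=42 was based. Modelling T0 with arm-specific means costs 25% to 33% of the achievable variance at rho=0.5, and less as rho rises.

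The figures assume complete data, 21 per arm and equal correlations. Actual arm sizes under a coin flip, and the losses that the article reports, would change them somewhat. The conclusion does not extend to an invalid interaction test or to a 10% rate of false efficacy claims. The change should be made before the analysis, which the article says follows its publication.

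**What to change.** 1. Delete group effects as a trigger for post hoc testing, and do not interpret the main effect averaged over T0, T1 and T2.
2. Fit T0, T1 and T2 as responses with one common baseline mean for both arms (a constrained longitudinal model: time, plus treatment terms at T1 and T2 only). Alternatively, use T1 and T2 as responses with T0 as a covariate.
3. Name one main treatment contrast per outcome, for example the baseline-adjusted difference at T1 or the average of T1 and T2, and report it with a 95% CI. Label the remaining contrasts, including the interaction, as secondary.

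The cost is analysis wording and a few lines of syntax; no new data are needed. The two models differ in one practical respect. With T0 as a covariate, participants who have no post-baseline score leave the model. The abstract reports 34 of 42 with a post-treatment evaluation, so this could affect up to 42−34 = 8 people, and the plan promises to include all randomised adolescents. The constrained form keeps them.

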### Efficacy Outcomes

A total of 9 outcome measures will be used to test preliminary evidence of training efficacy. Specifically, 7 self-assessed outcome measures (ie, 5 questionnaires for parents and 2 questionnaires for adolescents), 2 performance-based tasks assessing social cognition taken from a standardized neuropsychological battery, and a virtual reality–based assessment of everyday setting EF will be used. Questionnaires will be sent to patients and families in a sealed envelope; after completing them, participants will be required to return them to the research staff using an envelope with a postmark included in the sealed envelope within 2 weeks. The performance-based subtests assessing social cognition and the virtual reality–based assessment will be administered remotely using the Google Meet videoconference platform.

A detailed description of outcome measures is provided in Textbox 4. The sample of this study will include adolescents aged 11 to 19 years, but some measures and questionnaires have been standardized for populations having a lower maximum age range; however, they will be adopted for this study as no other measures with the same characteristics are available in the Italian language. The individual measures affected by this problem are clearly described in Textbox 4.

All outcome measures will be administered at T0 (ie, preintervention assessment), T1 (ie, immediately after the 6-month intervention), and T2 (ie, 6 months after the end of the intervention).

For the questionnaire outcomes, approaches to missing individual items will follow the guidelines for missing item procedures indicated in the manual for each questionnaire. If no guidelines for individual missing items are available, the mean of the completed items will be used to replace missing items if ≤10% are missing.

A summary of outcome measures to test training efficacy is presented in Textbox 5.

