### Conclusions

If this phase-2 RCT yields positive results, a larger, multicenter, phase-3 RCT could be planned and delivered to examine I-TOPS intervention efficacy and cost-effectiveness in a larger sample. Since 2020, Italy has a network for sharing the best practices related to rehabilitation for pediatric neurological children—Rete Pediatrica degli IRCCS [78]—with an important focus on telerehabilitation. This network could enroll in the phase-3 RCT, particularly given that the institute conducting the phase-2 RCT is part of this network.

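### Visit-specific comparisons are planned only after a significant interaction or group effect, so the T1 and T2 between-arm differences are not planned for every outcome and are exaggerated where they are followed up

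*Protocol article*

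**What the plan says.** The Abstract (Methods) and the Objectives place the efficacy assessment immediately after training and at 6-month follow-up, in two randomised arms. Efficacy Outcomes lists nine measures, used "to test preliminary evidence of training efficacy".

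Under Data Analysis Plan, each outcome goes separately into a linear mixed model with time (three levels), treatment and their interaction. The step from that model to specific comparisons is one sentence: "Significant interaction effects (ie, time and group) or group effects will be analyzed by post hoc tests". The threshold is also given: "The significance threshold will be set at <.05". The article does not say what the post hoc tests compare.

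Sample Size and Power Calculation cites a "small-to-medium average effect size (Hedges *g*=0.37") from a meta-analysis of the original programme. It then chooses, as a conservative value, "to estimate a small effect size of f=0.2" and concludes that "a sample size of 21 participants per group will be required to obtain 80% of power".

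On what follows, the Conclusions say: "If this phase-2 RCT yields positive results, a larger, multicenter, phase-3 RCT could be planned".

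**The concern.** Two questions are posed (the between-arm difference at T1 and at T2), but the plan answers them only for outcomes that first pass an omnibus test. That has three consequences.

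- An outcome that misses the threshold has no planned T1 or T2 contrast. In a trial of 42, such an outcome may be read as showing no effect when the data are compatible with the effect the article cites.
- An outcome that passes is followed up because its observed differences were large. Estimates selected this way are on average too large.
- Because the post hoc tests are undefined, a significant interaction could be followed by before-after tests within each arm, which do not compare the arms.

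For a phase-2 trial seeking preliminary evidence, the size of each difference and its uncertainty are a large part of what the efficacy analysis can offer.

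**Working it through.** **Inputs from the article.** α = 0.05; 21 per arm, N = 42; three time points; "Assuming a correlation of 0.50 between repeated measures"; f = 0.2; g = 0.37; no attrition in the power calculation. Numbers seen (Abstract, Results): 34 at T1 (19 and 15) and 31 at T2 (18 and 13). The main Results section gives 34 at both visits; 31 is used here for T2.

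**Assumptions not in the article.** g = 0.37 is read as the between-arm difference in SD units; no difference at T0; equal variances and equal correlations; loss unrelated to outcome; effect either sustained (0, d, d) or linear (0, d/2, d).

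**1. The stated sample size reproduces.** For the group-by-time interaction, λ = f²·N·m/(1−ρ) = 0.04 × 42 × 3 / 0.5 = 10.08, with 2 and 80 df. Power is 0.803 (0.782 at N = 40). The test that was powered is therefore the interaction.

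**2. What f = 0.2 means in SD units.**
- Sustained: the between-arm differences, centred over time, are (−2d/3, d/3, d/3). Halving them gives the cell deviations, whose mean square is d²/18. So f = d/√18 and d = 0.2 × 4.243 = 0.85 SD.
- Linear: the mean square is d²/24, so d = 0.2 × 4.899 = 0.98 SD.

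Both are more than twice 0.37.

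**3. How often an outcome passes, at d = 0.37 sustained, complete data.**
- Interaction: f² = 0.37²/18 = 0.0076; λ = 0.0076 × 42 × 3 / 0.5 = 1.92; power 0.21.
- Group effect, averaged over T0, T1 and T2: mean difference 2 × 0.37/3 = 0.247. The variance of a person's three-visit mean is (1 + 2 × 0.5)/3 = 0.667, so SE = √(2 × 0.667/21) = 0.252. The ratio is 0.98 and power 0.16.
- Either test, treated as independent: 1 − 0.79 × 0.84 = 0.34, which agrees with simulation.

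**4. Size of the selected estimates.** Trials were simulated (40,000 per scenario). The mean baseline-adjusted difference among those that pass was divided by the true difference. Ranges run over complete data and the reported attrition.

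| True effect (r = 0.5) | Gate | Pass | Estimate ÷ truth |
|---|---|---|---|
| 0.37 sustained | interaction or group (as written) | 29-34% | about 1.5-1.6 |
| 0.37 linear | interaction or group | 21-26% | 1.6-1.8 |
| 0.37 sustained | interaction only | 18-21% | 1.9-2.0 |
| 0.37 linear | interaction only | 14-17% | 2.1-2.2 |
| 0.85 sustained (f = 0.2) | interaction or group | 86-92% | 1.04-1.07 |
| 0.85 sustained (f = 0.2) | interaction only | 72-81% | 1.10-1.15 |

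Further results under the written gate: 1.3-1.5 at d = 0.5 (r = 0.5); 1.4-1.7 at d = 0.37 with r = 0.7; 1.9-2.3 at d = 0.2 (r = 0.5).

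**5. Without the gate.** The same contrast, reported for every outcome, averages 0.37 when the truth is 0.37. With complete data the variance of a change score is 2(1 − 0.5) = 1, so SE = √(2/21) = 0.31 SD and the 95% half-width is about 0.61 SD. With the reported losses SE is 0.34-0.35 and the half-width 0.66-0.68. Even an observed difference of zero would have an interval of about −0.61 to 0.61, which contains 0.37.

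**The case against.** The strongest reply is that the sentence restricts only post hoc tests. The model is fitted to every outcome, and with baseline as reference its two interaction coefficients are themselves the between-arm differences in change at T1 and T2. A reader might infer that the trial will produce no effect estimate for most outcomes. The article does not support that: nothing says estimates will be withheld, and an analysis plan not shown may list what is tabulated. This stands, and the point is limited to which contrasts are planned.

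A reader might also infer that selected estimates are doubled. That holds at 0.37 SD only if the interaction alone is the gate. The written rule also admits group effects, which lowers the factor to about 1.5-1.8, and at the planning effect it nearly vanishes. This stands too, although f=0.2 is presented as a small and conservative choice beside g=0.37 while implying about 0.85 SD or more. Effects near 0.37 are therefore the more relevant case.

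Nor does the article say that these estimates will size a phase-3 trial. It says only that such a trial could follow positive results, so misleading a later trial is an inferred risk. Within-arm follow-up tests are likewise a possibility that the wording leaves open, not something stated.

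Finally, an omnibus test followed by post hoc comparisons is conventional, and feasibility is the first objective. Both are true. But the gating rule is stated in the article, not merely left out of it, and it does not match the T1 and T2 questions that the article sets. Admitting a significant group effect does not cure this, because that effect averages over T0, before any treatment.

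**Conclusion.** The concern holds in limited form. The article ties specific comparisons to a significant interaction or group effect and plans no T1 or T2 between-arm contrast for outcomes that miss the threshold. If the true difference is a sustained 0.37 SD with correlation 0.5, about two thirds of outcomes or slightly more (66-71%) would get no planned follow-up, and the rest would be overstated by about 50-60%. The overstatement is 60-80% if the effect builds linearly, and about 4-7% if the true effect is the sustained 0.85 SD implied by f=0.2. These factors depend on the assumed effect size, its shape over time, the correlation, and losses unrelated to outcome. The point is a worthwhile improvement to the analysis, not an error that invalidates the fitted model.

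**What to change.** Replace the significance-gated sentence with a planned analysis. For every efficacy outcome, whatever its interaction or group P value:

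- report from the mixed model the I-TOPS minus wellness difference in change from baseline at T1 and at T2, each with a 95% CI and a standardised size;
- name these two contrasts as the planned efficacy results, in place of the post hoc tests;
- state that within-arm changes are descriptive only.

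This needs two contrasts per outcome from the model already specified, in software already named, and no new data. The article says the analysis will follow publication of the protocol, so the wording could be settled before results are known. The downside is a longer results table in which most intervals are wide, with a half-width of about 0.6-0.7 SD. Planned reporting also does not stop later readers from singling out the favourable outcomes, but it leaves the full set in view.
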